## **5. Study Procedures**

### **5.1 Recruitment & Screening**

Arizona Liver Health Clinics will utilize their patient network to identify eligible patients and additional IRB approved recruitment methods may be utilized for patient recruitment. Most individuals are expected to be identified by providers during clinic visits who have a historic diagnosis of NAFLD or NASH. Patients are screened for interest in study participation. If interested, participants will be screened and guided through the informed consent process by a member of the research staff (see below). After providing informed consent, patients will receive a screening FibroScan. A CAP score < 300dB/m is considered a screen failure. Participants then complete a collection of baseline labs, biometrics, focused physical exam, BMI measurement, Treatment Orientation Call, and MRI-PDFF. PI reviews all data to determine participant eligibility for primary or secondary analysis groups.

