| Screening Procedures & Schedule of Assessments | 

1) Participants are pre-screened for a diagnosis of NAFLD or NASH, per medical record

2) Participants are screened for interest in study participation & eligibility.

3) After providing informed consent, participant completes initial FibroScan screening (CAP < 300dB/m is a screen failure).

4) Participant completes collection of screening labs, biometrics, and focused physical exam and is scheduled for MRI-PDFF and Treatment Orientation Call.

5) The participant will complete a Treatment Orientation Call with a Better Therapeutics' Product Support Specialist prior to using BT-NCBT-00x.

6) Participant completes MRI-PDFF.

7) PI reviews all data to confirm participant eligibility.

8) Participants who meet all inclusion and exclusion criteria will then be referred for initiation of treatment through the Better Therapeutics Study Portal.

a) Referral requires study staff to enter the patient's unique ID, mobile phone number, and email into the Better Therapeutics Study Portal.

9) The participant receives an email and text with a link to create an account and download the BT-NCBT-00x App.

a) Participants who do not complete App onboarding will be considered screen failures and will be replaced.

10) The participant completes 90-day behavioral intervention using BT-NCBT-00x.

11) The participant returns to clinic post-study visit for repeat Fibroscan, labs, biometrics and MRI-PDFF.

 |

|                           |                                                                                                                                                                                                                                                                                                                                                                                                                                                                                                                                                                                   |

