|                             |                                                                                                                                                                                                                                                                                                                                                                                                                                                                                                                                                                                                     |
|-----------------------------|-----------------------------------------------------------------------------------------------------------------------------------------------------------------------------------------------------------------------------------------------------------------------------------------------------------------------------------------------------------------------------------------------------------------------------------------------------------------------------------------------------------------------------------------------------------------------------------------------------|
|                             | 
and percentages. In addition, exact binomial confidence intervals for the true rates will be provided.
 
Safety Summaries
 
Treatment-emergent Adverse Events will be summarized using counts and percentages. A treatment-emergent adverse event (TEAE) will be defined as any AE that occurs after the start of use of the Better Therapeutics App. Summaries of AEs will include:
 

● All TEAEs

● Serious TEAEs

● TEAEs by severity and relationship to treatment

● and medical software incidents

 |
| Total Study Duration | 
Each enrolled participant will be exposed to a 90-day treatment intervention. The treatment begins from the day the participant downloads the App and completes onboarding and continues for the subsequent 90 days. The imaging required to evaluate primary endpoints must be completed within 14 days following completion of the intervention.
                                                                                                                                                                                                                                           |

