## 5.5 Product Support

A selection of patient services will be provided over the course of the study. Participants will be expected to complete two calls with a behavioral specialist: the Treatment Orientation Call will be completed prior to the start of intervention and a wrap-up call completed at the end of the intervention. The Treatment Orientation Call is intended to help introduce the participant to the nature of the treatment and assess readiness to engage in behavioral therapy. In this call, participants will also receive education on evidence-based behavioral strategies for NAFLD treatment that are not yet fully integrated into BT-NCBT-00x, such as the benefit of reducing dietary intake of saturated fat and replacing with monounsaturated and polyunsaturated fatty acids. The wrap-up session is intended to allow the Better Therapeutics team to gather feedback about participants' experiences using the intervention.

The study population will also be monitored by a Nurse Practitioner to assess participants' engagement and biometric progress. Users who are not meeting expected thresholds for engagement or biometric progress will be offered additional support in the form of a call with a behavioral specialist or nurse practitioner to help identify barriers to behavioral therapy and develop a plan for addressing these potential obstacles to improve treatment adherence and efficacy. Sample screen images of support messages and call scheduling ability in the App can be seen in Appendix 17.3.

A product support specialist will be available over the length of the study to provide support for participants who need help using BT-NCBT-00x. If a participant's needs are beyond the scope of technical product support, the product support specialist will refer the participant to the clinical care team for behavioral support. In addition, a behavioral support specialist may proactively reach out to patients to offer more support to help them get the most out of using BT-NCBT-00x. Participants will be free to accept or turn down any offer of support.

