### 11.1 Primary and Secondary Endpoint Analyses

The primary efficacy endpoint is the change in percent liver fat as measured by MRI-PDFF from baseline to 3 months after enrollment. The results at baseline, at 3 months post-enrollment, and the change from baseline will be summarized descriptively. Change from baseline results will be calculated as (post-baseline minus baseline). The baseline result is defined as the last assessment prior to starting the Better Therapeutics App. In addition, the change from baseline in the percentage liver fat will be tested using a one-sample t-test if the normality assumption is met. The normality assumption will be assessed using the Shapiro-Wilks test for normality. If the normality assumption is not met, then the change from baseline will be tested using a Wilcoxon rank sum test.

The continuous secondary endpoints will be summarized in the same manner as described for the primary efficacy endpoint.

The categorical secondary endpoints, such as the percentage of participants who achieve  $\geq 30\%$  reduction in MRI-PDFF from baseline to post-intervention, will be summarized using counts and percentages. In addition, exact binomial confidence intervals for the true rates will be provided.

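### The baseline MRI-PDFF is listed after the Treatment Orientation Call, which already teaches NAFLD dietary strategies, and no rule stops a post-call scan from serving as the primary baseline

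*Protocol*

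**What the plan says.** The Protocol Synopsis, under Screening Procedures & Schedule of Assessments, numbers the screening steps. FibroScan is step 3. Labs, biometrics and the physical exam are step 4, where the participant also "is scheduled for MRI-PDFF and Treatment Orientation Call". Step 5 reads "The participant will complete a Treatment Orientation Call with a Better Therapeutics' Product Support Specialist prior to using BT-NCBT-00x". Step 6 reads "Participant completes MRI-PDFF". Eligibility review by the principal investigator (PI) is step 7, and referral and the App link follow. Section 5.1 gives the same order in running text: "Participants then complete a collection of baseline labs, biometrics, focused physical exam, BMI measurement, Treatment Orientation Call, and MRI-PDFF", and then PI review.

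The call has treatment content. Section 5.5 says: "In this call, participants will also receive education on evidence-based behavioral strategies for NAFLD treatment that are not yet fully integrated into BT-NCBT-00x". The example given there is changing the type of dietary fat. The Synopsis repeats this under Study Design.

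The timing definitions are these:
- Section 5.5: "the Treatment Orientation Call will be completed prior to the start of intervention".
- Synopsis, Total Study Duration: "The treatment begins from the day the participant downloads the App and completes onboarding".
- Section 11.1: "The baseline result is defined as the last assessment prior to starting the Better Therapeutics App".
- Table 1: the MRI comes after FibroScan and, by footnote X2, before referral to treatment. For the call, only its scheduling is tabled.

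**The concern.** The primary endpoint is change in liver fat, and diet is one of the behaviours the therapy targets. If participants hear dietary advice for NAFLD and are scanned afterwards, whatever they have already changed by the scan date sits in the baseline and drops out of the measured change.

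Three things are at stake:
- **The primary estimate.** The measured reduction would be smaller than one taken from a scan before the call. Section 1 says the study is meant to help plan future studies, so the estimate matters as well as the test.
- **Comparison between measures.** The Synopsis objectives include exploring how sensitive imaging, composite scores and serum markers are to behavioural change. FibroScan, labs and weight are listed before the call and MRI-PDFF after it, so their baselines would not be aligned.
- **Membership of the primary set.** The baseline scan also decides who meets PDFF ≥10%. A participant near the cut-off could fall on the other side of it because of an early response.

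**Working it through.** **1. Which orders the Protocol allows.** The binding timing rules are few:
- the call comes before App use (Synopsis step 5; Section 5.5);
- the MRI comes after FibroScan (Table 1);
- the MRI comes before referral (Table 1, footnote X2);
- baseline is the last assessment before App start (Section 11.1).

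Both call-then-MRI and MRI-then-call satisfy all four. The two procedural lists show only call-then-MRI, so staff who follow them in order will scan after the call. No maximum or minimum interval between the two is stated.

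**2. Direction of the effect.** Let g be the mean reduction in liver fat between call and scan, and D the mean reduction from scan to end of treatment.
- Scan before the call: measured reduction = g + D.
- Scan after the call: measured reduction = D.

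The difference is g. If the education works at all, g ≥ 0, so the bias is toward no change. The Protocol gives neither the interval nor any effect of the call, so g cannot be computed.

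**3. The plan's own sample size, reproduced.** Inputs from Section 9: mean change -2.4, SD 1.6, alpha 0.05, about 8 participants for about 90% power, 20% attrition. Sidedness is not stated; two-sided is assumed here.
- Standardised effect: 2.4 / 1.6 = 1.5.
- Power of the one-sample t-test comes from the noncentral t distribution with n - 1 degrees of freedom and noncentrality 1.5 × √n. For n = 8 this is 1.5 × 2.83 = 4.24.
- Result: 90.8% at n = 7 and 95.1% at n = 8. A simulated exact Wilcoxon signed-rank test (4,000 runs, normal data) gives 91.6% at n = 8.
- Attrition: 8 / (1 - 0.20) = 10, as stated.

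The stated 8 and 10 are reproduced, and neither changes if the MRI is moved ahead of the call.

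**4. What a loss would cost (illustration only).** Suppose a share f of the planned 2.4 points occurs before the scan, so that the measured effect is 2.4 × (1 - f), with SD 1.6 and the same two-sided t-test.

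| f | Measured effect | Power, n = 8 | Power, n = 10 |
|---|---|---|---|
| 0 | 2.40 | 95.1% | 98.7% |
| 5% | 2.28 | 93.0% | 97.9% |
| 10% | 2.16 | 90.3% | 96.6% |
| 20% | 1.92 | 82.8% | 92.0% |
| 30% | 1.68 | 72.2% | 83.9% |
| 50% | 1.20 | 44.9% | 56.2% |

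With 8 evaluable participants the stated 90% survives a 10% loss but not a 20% loss. Nothing in the Protocol says which row applies.

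**The case against.** The strongest case against has five parts.

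- **By definition the baseline is clean.** A reader might infer that the baseline scan is taken once the intervention is under way. The Protocol does not support that. It places the call before the intervention, starts treatment at App onboarding and requires the MRI before referral. This stands: on the Protocol's own terms the scan always precedes treatment. What remains is exposure to educational content that the Protocol does not count as treatment.
- **The order is listed, not mandated.** Section 5.1 is a running list, step 4 names the MRI first when both are booked, and Table 1 does not time the call. This also stands, so some participants may be scanned first. A mixture of orders is not reassuring, however, because the baseline would then mean different things for different participants.
- **The bias is conservative.** This is true for the hypothesis test. It does not help an estimate intended for planning.
- **A scan after the education isolates the App better.** The Protocol gives no such rationale. It would hold only in part, because advice given before the scan can go on acting during the 90 days.
- **The call has a screening role.** It also assesses readiness for behavioural therapy, which may inform PI review. This is a fair reason to leave the call before that review, but not a reason to put it before the MRI.

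A reader might also try to size the effect by spreading the 2.4 points evenly over 90 days and multiplying by a guessed gap in days. That fails. The full 90-day App period still follows the scan, so on that model the change after the scan is still 90 × (2.4 / 90) = 2.4, and the planned effect is untouched. The model also credits one call with the daily rate of the whole programme, and the gap is not in the document.

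**Conclusion.** The point holds in a limited form. As listed, the procedures put the baseline MRI-PDFF after a call that delivers dietary education for NAFLD, and neither the baseline definition nor Table 1 prevents this. The possible consequences are a bias toward no change in the primary endpoint, a PDFF baseline out of line with the FibroScan, lab and weight baselines, and some effect on who meets the PDFF ≥10% cut-off.

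The size cannot be determined from the document, and it may be small if the gap is short or one call changes little. The power table shows only that a loss of up to about 10% of the planned effect would leave the stated power intact at n = 8. It assumes a two-sided t-test, SD 1.6 and a total reduction fixed at 2.4. The sample size itself is not in question. The change is worth making because it costs almost nothing and the order cannot be repaired once the scans are done.

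**What to change.** 1. In Synopsis steps 5 and 6 and in Section 5.1, list the baseline MRI-PDFF before the Treatment Orientation Call.
2. In Table 1 footnote X2, add that the MRI is done before the call as well as before referral.
3. Leave the call before PI review, so that its readiness assessment remains available.
4. If a scan nevertheless follows the call, keep it as the baseline and record the dates of both. The Section 11.1 definition need not be re-anchored to the call; doing so would leave such a participant without a PDFF baseline, in a primary set of only about 10.

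The cost is two reordered lists, one footnote and two recorded dates. The call may be booked a few days later, and no sample-size figure changes.

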## 5.2 Informed Consent Process

A properly executed informed consent will be obtained from each participant prior to any study-specific activities being completed. Delegated staff at the study site will facilitate the informed consent process with eligible participants. Potential participants will have the option of contacting study personnel with any questions or concerns before providing a signature on the consent. Participants will be provided a physical copy of their signed consent form. Participants will be able to withdraw from the study at any time by emailing or calling study personnel using the contact information provided in this form.

## 5.3 Study Enrollment

Participants who are consented and eligible for participation will be referred by the study site to begin treatment with the BT-NCBT-00x study App. Referral requires clinic staff to enter the patient's unique ID, mobile phone number, and email into the Better Therapeutics Study Portal. The portal is secure and HIPAA compliant.

Once referred, the participant will receive an email and text with link directing them to a secure website to create an account for the study intervention (see Appendix 17.1). Account creation will require participants to provide an email address, mobile phone number, first name and last name. This information will be validated against the values added to the Study Portal by the Arizona Liver Health delegated staff to confirm the App is being downloaded by the correct individual. The creation of the account triggers an SMS with a link to download the App from the app store appropriate to the phone type. Enrollment in the study will be completed once a participant completes the self-directed onboarding within the App. Participants who do not complete App-onboarding will be considered screen-failures and replaced.

## 5.4 Behavioral Intervention

BT-NCBT-00x was created by the Sponsor, Better Therapeutics, Inc. It delivers treatment to participants with cardiometabolic disease, using behavioral therapy that targets individuals' beliefs and behaviors related to improving dietary quality and physical activity. Sample screen images of digital therapeutic can be seen in Appendix 17.2.

BT-NCBT-00x is accessed via the participants' smartphone after downloading from the phone's corresponding app store. The mobile app that study participants will download for the study is called "Better" in the app stores.

The behavioral intervention process involves: 1) identifying maladaptive thoughts based on misinformed or false underlying core beliefs (e.g., those related to macronutrient fears, the hedonic nature of eating, physical exertion, other perceived barriers to changing lifestyle) that

lead to disease-promoting behaviors; 2) replacing these maladaptive core beliefs and thought patterns with adaptive ways of thinking developed from rational reflection; 3) providing collaborative (between participant and device) construction of behavioral exercises to test core beliefs; and 4) using additional validated behavioral techniques to enhance a participant's capacity to solve problems, plan activities and cope with interfering emotions or thoughts. BT-NCBT-00x helps participants understand the steps they should prioritize by presenting them with a treatment plan that summarizes their daily and weekly goals.

Each week, BT-NCBT-00x asks participants to complete a new behavioral module, along with one or more skill-based exercises that are related to that week's module. All participants are exposed to the same course of modules. The modules are expected to take between 10-20 minutes to complete. The modules are called "lessons" within BT-NCBT-00x. Each lesson addresses core beliefs in one of the following areas:

- Personal beliefs and barriers, such as those related to a participant's ability to change and control his or her behaviors;
- Beliefs about macronutrients and the importance of various food types;
- Hedonic-related beliefs about pleasant or unpleasant sensations experienced by eating or exercising; and
- Beliefs about exercise.

Skill exercises are intended to provide an opportunity for participants to practice skills related to behavioral beliefs. The method by which participants must practice these skills is designed to enhance executive function tasks such as planning, problem solving and goal setting. Each lesson explains the rationale and benefits of the skill exercise in reference to the core topic being explored.

In addition to completing a lesson (and one or more skill exercises), BT-NCBT-00x directs patients to self-report diet and exercise behaviors, medication adherence, and biometrics (e.g., weight). If the patient has comorbid Type 2 diabetes or hypertension, he or she will also be able to self-monitor fasting blood glucose and blood pressure each day. Weekly behavioral goals, including diet and exercise behaviors, are determined through a goal setting exercise, and are advanced in a manner most likely to maintain or increase self-efficacy. When self-efficacy is high, the participant has a high probability of achieving his or her goals.

Participants will be directed to engage with one lesson each week of the study, to report plant-based meals consumed and minutes of exercise completed and, if indicated, to measure

their blood glucose and/or blood pressure daily. All participants will be given access to the App for 3-months.

## 5.5 Product Support

A selection of patient services will be provided over the course of the study. Participants will be expected to complete two calls with a behavioral specialist: the Treatment Orientation Call will be completed prior to the start of intervention and a wrap-up call completed at the end of the intervention. The Treatment Orientation Call is intended to help introduce the participant to the nature of the treatment and assess readiness to engage in behavioral therapy. In this call, participants will also receive education on evidence-based behavioral strategies for NAFLD treatment that are not yet fully integrated into BT-NCBT-00x, such as the benefit of reducing dietary intake of saturated fat and replacing with monounsaturated and polyunsaturated fatty acids. The wrap-up session is intended to allow the Better Therapeutics team to gather feedback about participants' experiences using the intervention.

The study population will also be monitored by a Nurse Practitioner to assess participants' engagement and biometric progress. Users who are not meeting expected thresholds for engagement or biometric progress will be offered additional support in the form of a call with a behavioral specialist or nurse practitioner to help identify barriers to behavioral therapy and develop a plan for addressing these potential obstacles to improve treatment adherence and efficacy. Sample screen images of support messages and call scheduling ability in the App can be seen in Appendix 17.3.

A product support specialist will be available over the length of the study to provide support for participants who need help using BT-NCBT-00x. If a participant's needs are beyond the scope of technical product support, the product support specialist will refer the participant to the clinical care team for behavioral support. In addition, a behavioral support specialist may proactively reach out to patients to offer more support to help them get the most out of using BT-NCBT-00x. Participants will be free to accept or turn down any offer of support.

